### Study Population and Recruitment

### Children between six months and five years who present to a CHW at the community health post with fever and/or cough/difficult breathing will be assessed, classified and managed. Six months was selected as the cut off because Coartem® is not recommended for younger children weighing less than 5 kg and also because of the difficulty of assessing very young children for pneumonia. Children outside this age range and adults will be managed according the current treatment guidelines for CHWs and will not be followed up by study personnel. Any child with severe illness or signs of severe malaria or pneumonia will be referred as per standard of care and excluded from enrollment into this study.

###### Inclusion criteria:

Children with the following characteristics will be considered for study inclusion:

- Age between 6 months and 5 years
- Present to CHW with history (reported) of fever.

### Present to CHW with cough or difficult breathing

### *Exclusion criteria:*

Children with any one or more of the following conditions will be excluded:

- Age below 6 months or above 5 years
- Presence of signs and symptoms of severe illness
  - Convulsions
  - abnormally sleepy or coma
  - persistent vomiting
  - unable to drink or feed
  - chest in-drawings
  - severe pallor
- Known sensitivity to Coartem® and/or amoxicillin

The CHWs will keep register of all patients seen as part of standard care. From this register, the CHWs will extract information to complete identification and baseline form for every child with fever or/and fasting breathing. This form will be used by data collectors to locate patients for the follow-up visits and also to measure the accuracy of classification and appropriateness of treatment.

In the intervention arm, children 6 months to 5 years whose caregivers refuse RDT testing will not be followed up. However, we will keep track of them and measure the proportion of RDT refusals.

The option for a caregiver to go to a health facility to receive care in place of being cared for by the CHW is an accepted norm in the communities. However, existing community based health educators in the area (NHCs, child survival facilitators, community based distributors, traditional birth attendants, growth monitors) in their interaction with community members will emphasize that they have this option.

### 4.5. Roles and responsibilities of community health workers

The primary role of the CHWs is to serve as the households’ first point of contact with the health system. They will classify the child’s illness and provide specific drug treatment.

The key responsibilities will include:

- taking a history from the caretaker
- assessing the child including respiratory rate, temperature and the presence of danger signs;
- treating or referring as appropriate
- dispensing specific medication and observing the child taking the first dose
- providing the caretaker with instructions for the remainder of the treatment course, as well as for care of the sick child in the home.
- counseling caregivers to return if condition deteriorates or experience any adverse effects
- conveying a sense of urgency to the caretaker when a referral is indicated, administering start dose of medication if indicated, and providing a referral slip.
- managing a stock of medications and supplies
- maintaining simple records and registers
- conducting community education

In the intervention arm, the CHWs will also perform and interpret RDTs

#### 4.6 Minimum requirements for CHWs

CHWs involved in this project must be literate, numerate, and able to write and manage simple calculations. After training, they must be competent in assessing respiratory rate and recognizing danger signs, and following the management classification charts. They must be acceptable to caregivers as well as to communities. CHWs must be available and willing to see patients outside regular hours in cases of emergency. Finally, they must be honest and willing to follow the protocol.

**4.7 Training of community health workers**

The CHWs will be trained to classify and treat children with pneumonia or malaria or both and also manage stock of appropriate drugs and supplies. The CHWs in the intervention areas will also be trained to perform RDTs. They will also require skills to be able to accurately complete the relevant registers and data collection forms as well as counseling of caregivers and general health education. The training will last for one week and a training manual will be developed for this purpose. The training manual will be adapted from Zambia’s “Community Health Workers’ Handbook: A Reference Manual for the Community Health Workers”. The training will be conducted by a training team experienced in IMCI skills training and will be drawn from both Mazabuka and Siavonga districts with support from the Provincial CHW training team. The training will be conducted in groups of 15-20 at Chikankata hospital.

The training course will cover the following elements:

- taking basic clinical history
- basic examination skills with emphasis on counting respiration, assessing lower chest in-drawings and taking temperature
- recognition of general danger signs, classification of sick child according to the classification system for malaria and pneumonia
- treatment – including side effects of the drugs
- performing and interpreting RDTs.
- referral procedures
- provision of instructions and counseling to caregivers (including home care, referral, importance of completion of course of drugs, need to give Coartem**®** with fatty meal )
- drug stock management
- record keeping

The training will use a variety of methodologies including lectures, presentations, discussions, case studies, demonstrations, practice, role-plays, and video shows. The CHWs will take quality time to go through and practice the use of a diagnostic tool that will be developed to assist them to classify cases. The trainer/supervisors will follow up the CHWs one month after the initial training to ensure that they acquired the necessary skills. There will be refresher courses every six months and will last 2 days.

There will be a half day session for the intervention CHWs on hands-on introduction to RDT use. This will cover performing and interpreting the test – cleaning the finger with swab, pricking with a lancet, drawing blood with the pipette, squeezing the blood from the pipette into the well, adding the buffer and reading the results. The training will also cover the need to maintain aseptic techniques and to protect themselves from being pricked with the lancet; and disposal of waste products including the lancet, pipette, and device. They will also be taken through procedures of what to do if they accidentally prick themselves including immediate washing of wound with antiseptic soap and plenty of water.

CHWs in the Philippines and Laos have been trained to perform and interpret RDTs using job aids with great success23.

#### 4.8 Training of health center personnel in IMCI

In order to support and supervise the CHWs during the implementation of the study, rural health center personnel in the study area will undergo full IMCI training. The study will support this training because theongoing IMCI training for all health personnel by the MOH in the country has been lagging behind in the Southern Province where the study area is located. This will also enable them to deal effectively with cases that will be referred from the CHWs. The training will cover classification and management of IMCI diseases, supervisory and monitoring skills including monitoring of drug use by the CHWs. The training will also cover their role and responsibilities in the data capture system that will be developed to capture data at the health facilities to measure some of the study outcomes. The Provincial IMCI Training Team and the study coordinator will conduct the training.

**4.9 Training of Data collectors and Data Supervisors**

This study will use 12 data collectors (DCs) (2 per cluster) and 2 data supervisors (DS). Each DS will be responsible for 6 DCs. The DCs and the DS will be trained to be able to conduct the follow-up visits and collect data using the case report forms that will be developed. They will be trained to take basic clinical history and perform basic examination skills with emphasis on counting respiration, assessing lower chest in-drawings and taking temperature. The training will also cover the protection of human subjects and confidentiality. The training will provide the data team with the necessary communication and interviewing skills so that they can conduct successful interviews and collect useful data. During the training, the participants will be taken through the case report forms question by question, explaining each thoroughly and detailing the information required. Training methods that will be used will include, discussions, practice and role plays. The case report forms will be translated into the local language and piloted during the final days of the training. The training will last five days. The training will be conducted by a team, made up of [name] (PI) and the two Zambian Co-investigators.

Four others will be trained as DCs but will be put on “shelf” and only be used to replace any of the twelve whose performance falls below expectations or who resigns during the course of the project. All the trainees will be given a training allowance.

#### 4.10 Development of appropriate treatment algorithm and job aids

Appropriate treatment algorithm and job aids will be developed to aide the CHWs to classify and manage pneumonia and malaria. These tools will be adapted from existing tools and piloted before their use. The tools will walk the CHW systematically through what he/she should ask or look for and the action that needs to be taken. The job aids will include a chart of danger signs (very sick child) and how to perform and interpret RDTs based on the manufacturer’s instructions. The training of the CHWs will emphasize the use of these tools.

#### 4.11 Drug Supply and Management

Currently, CHWs receive community health worker kits prepared by the Central Medical Stores in Lusaka through the districts and the rural health centers. In the Chikankata Health Services area, CHWs in RHC catchment areas of Mazabuka collect their kits from Chikankata Hospital after the latter has collected them from the Mazabuka DHMT. In few cases, the RHC staff collects the kits from Chikankata Hospital and distributes them to the CHWs. For CHWs in RHC catchment areas of Siavonga, they get their supply from Siavonga DHMT through the RHCs. But sometimes they collect the kits from the Chikankata Hospital.

For the purpose of this study, both the Mazabuka and Siavonga DHMTS have agreed to streamline the supply system. Both DHMTs will allow CHS to distribute the kits to the CHWs. This means that CHS will collect the kits from the respective DHMTs and stock them at the Chikankata Hospital from where it will be distributed to the CHWs. The Coartem**®,** amoxicillin and the RDTs will be packaged as a supplementary pack at Chikankata Hospital under the supervision of the hospital pharmacist and distributed to the CHWs with the standard community health worker kit on a monthly basis. The Coartem**®,** amoxicillin and RDTs will come from the usual MOH source for supplying health centers.

Inventory forms will be designed to monitor the supply of medicines and RDTs. Even though CHWs will be supplied on a monthly basis, restocking of essential medications and supplies will occur from Chikankata hospital if the CHW runs out. The RHCs staff responsible for supervision will hold a 1 – 2 month buffer stock of the drugs and RDTs and will restock a CHW’s supply if the need arises during supervision. This system is intended to avoid stock-outs. There will be special section during the training of CHWs on drugs and RDTs management and storage as well as dosing of drugs.

The Study team shall collaborate with the MOH and DHMTs to ensure that the health facilities in the study area have Coartem**®,** amoxicillin and RDTs in stock.

**4.11.1 Rationale for choosing Amoxicillin**

The decision to use amoxicillin was made in conjunction with the IMCI unit of the Zambian MOH. We chose amoxicillin based on the comparative therapeutic advantages and disadvantages of several candidate antibiotics, local patterns of use, and restrictions on the categories of antibiotics that can be used in community settings according to current Zambian health policies. It is one of the drugs recommended by the Zambia National treatment guidelines for pneumonia. Amoxicillin has a long safety record, is readily available in Zambia, is inexpensive, widely accepted by patients and clinicians, and has excellent bioavailability when taken orally.

The very few serious side effects to amoxicillin that occur are due to hypersensitivity. Since it will be given in an oral form, this form of reaction is not anticipated. Less acute reactions, respiratory and skin manifestation including tightness in the chest, itching and urticaria rash may occur and we will look out for them.

We are considering the use of tablets over syrups as tablets offer advantages over the syrup, which include lower cost, easier dosing, easier ability to comply, and ease of packaging and distribution.

Treatment Chart

| Weight | Age | Dose | Total dose |
| --- | --- | --- | --- |
| 4-9 kg | 6-11 months | ½ tab 3x/day  5ml (1tsp) 3x/day | 4½ tabs  45 ml |
| 10-19 kg | 12 m – 5yrs | 1 tab 3x/day  10ml 3x/day | 9 tabs  90 ml |

**4.11.2 Rationale for choosing Coartem® (artemether - lumefantrine)**

Coartem**®** is currently the first line anti-malarial drug in Zambia for the treatment of uncomplicated malaria. The Zambian MOH has just decided to deploy Coartem® to the community level. It is a fixed combination of two antimalarials, artemether and lumefantrine. It has been proven through clinical trials to be highly efficacious. It eliminates parasites and symptoms significantly faster than most current anti-malarial medications and prevents progression to fatal cerebral malaria. It is rapidly gametocidal, thus helping to reduce transmission while achieving a high cure rate. It’s clinical cure rate is 95% to 97 % in areas with multidrug resistant *falciparum* infection. It is well tolerated showing no evidence of organ or system specific toxicity. It is well tolerated by children (including children between 5 and 10 kg) and can be used in people with renal or hepatic impairment. It will be prescribed according to the manufacturer’s guidelines and in a manner consistent with the Zambian National guidelines. Adverse effects are mostly mild include abdominal pain, anorexia, asthenia, myalgia and arthralgia. In a few cases, children may develop a cough, some pruritis and a rash but none of the adverse events are found to represent a safety problem.

The MOH is planning to procure generic artemether-lumefantrine and when this happens, Coartem® will be replaced with the generic artemether-lumefantrine.

Treatment Chart

| Weight | Age | Dose | Total dose |
| --- | --- | --- | --- |
| 5-14 kg | 1-5 yrs | 1 tab twice a day | 6 tabs |
| 15-24 kg | 5 – 9 yrs | 2 tabs twice a day | 12 tabs |

- - 1. **ICT Malaria Pf as the choice of RDTs**

The ICT Malaria Pf is currently the RDT in use in Zambia. The MOH has procured and distributed ICT Malaria Pf for use in public health facilities. ICT Malaria Pf is a rapid, qualitative two site sandwich immunoassay for the detection of *P. falciparum* specific histidine rich protein -2 (Pf HRP-2) in whole blood. It is both sensitive and specific test for the detection of *P. falciparum* malaria. It is easy to perform and interpret. It has improved stability and the kit can be stored between 4-37°C till the duration of the shelf life. If in the course of the study, the MOH procures another type of RDT, the study will switch to the new type accordingly. There is the possibility that a test can be false positive and therefore a child with malaria may not receive malaria treatment. This condition may worsen. CHWs will counsel caregivers to report back if condition does not improve or worsens.

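### The Coartem dose chart in Protocol 4.11.2 does not fit the eligible age range: it has no age entry for 6-11 months, and exactly 5 years falls in both rows.

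*Protocol*

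**What the plan says.** The inclusion criterion is "Age between 6 months and 5 years" and the matching exclusion is "Age below 6 months or above 5 years", so a child of exactly 5 years is not excluded. The section on study population and recruitment links the lower limit to Coartem itself: "Six months was selected as the cut off because Coartem® is not recommended for younger children weighing less than 5 kg". Infants from 6 months are therefore meant to be treatable with it.

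Section 4.11.2 then prints a two-row Coartem chart:

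- "5-14 kg | 1-5 yrs | 1 tab twice a day | 6 tabs"
- "15-24 kg | 5 – 9 yrs | 2 tabs twice a day | 12 tabs"

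The text above the chart says that prescribing follows the manufacturer and is to be done "in a manner consistent with the Zambian National guidelines". The amoxicillin chart in 4.11.1 does have an infant row: "4-9 kg | 6-11 months | ½ tab 3x/day". Section 4.10 says that the treatment algorithm and job aids for CHWs are still to be developed.

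**The concern.** The eligibility criteria and the Coartem chart are both written in ages, and the ages do not match at either end. At the lower end the chart's age column begins six months after eligibility does. At the upper end the two rows share the age of 5, and the rows differ twofold in dose.

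What is at stake is the clarity of a dosing instruction for young children. CHWs dispense Coartem in both arms: after a positive rapid test in the intervention arm, and for febrile illness under the IMCI guidelines in the control arm. Section 9.2 acknowledges that CHWs are not used to prescribing the study drugs and that misuse is possible. The CHW tasks listed in 4.5 and the register fields listed in 5.1 include age but not weight, so age may well be the column a CHW reads. If the chart went into the job aids as printed, a CHW working from age would find no entry for an eligible infant and two entries for a child of exactly 5.

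**Working it through.** No sample size, power or error-rate figure is involved. The check sets the chart against the eligibility range.

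**Are the printed rows coherent?** The chart gives no course length, but one can be backed out as total tablets divided by tablets per day.

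- Row 1: 6 / (1 × 2) = 3 days.
- Row 2: 12 / (2 × 2) = 3 days.

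Both rows imply the same 3-day course, so the dose cells agree with each other and the rows do not look damaged in transcription. The mismatch is in the age cells.

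**Each eligible age against the chart**

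| Age | Row matched by age | Course by age | What weight adds |
| --- | --- | --- | --- |
| 6-11 months | none | none | the 5-14 kg band gives 6 tablets |
| 1 year to under 5 years | row 1 | 6 tablets | not needed for a reading by age |
| exactly 5 years | rows 1 and 2 | 6 or 12 tablets | would settle the row, if known |

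**Size of the gap at the lower end.** Months 6 to 11 are 11 − 6 + 1 = 6 age-months. Months 6 to 59 are 59 − 6 + 1 = 54. The age column is silent for 6 / 54 = 11% of that age span. This is a share of the age range, not of the children; the protocol gives no age distribution.

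**Size of the conflict at the upper end.** 12 / 6 = 2 per course, and per day (2 × 2) / (1 × 2) = 2. It arises at one boundary age.

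**Is there a competing dose for infants?** No. Row 1 starts at 5 kg and is the lowest dose printed, and 4.11.2 describes the drug as well tolerated in children of 5 to 10 kg. The only dose the chart offers an infant of 5-14 kg is 1 tablet twice a day. The gap is a missing label, not a choice between two doses.

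**Does it reach a primary outcome?** Section 3.4 defines the Coartem outcome as the proportion of febrile children treated with the drug. A child counts the same with 6 tablets or 12. The other primary outcome scores amoxicillin, which has its own chart with a 6-11 month row.

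**The case against.** The strongest reply is that the chart is not the working instrument. It sits in a rationale section that defers to the manufacturer and to national guidelines. The algorithm and job aids are still to be written, adapted from existing tools and piloted (4.10, 5.3), and training is adapted from the national CHW handbook (4.7). For infants the weight band leaves only one dose. For the upper boundary, the protocol elsewhere describes its population as children under five, which suggests that the first row was meant to stop short of 5.

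Most of this stands and is why the point is minor. It does not remove the point. This is the only Coartem dose table in the protocol, its age cells do not match the eligibility criteria, and those criteria exclude only children above 5.

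A reader might go further in three ways that the documents do not support:

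- **A wider conflict between age and weight.** The amoxicillin chart pairs 10-19 kg with 12 months to 5 years, while the second Coartem row starts at 15 kg, so a 1-4-year-old of 15-19 kg might seem to have two Coartem doses. That needs both columns in use at once and rests on the broad bands of another drug's chart. The protocol gives no weights to show that such children are expected.
- **An uncovered 4 kg infant.** The amoxicillin infant row reaches down to 4 kg, below the Coartem floor. The recruitment section already says that Coartem is not recommended under 5 kg, so this adds little.
- **CHWs cannot weigh children.** The lists in 4.5 and 4.7 are not closed, and the contents of the identification and baseline form are not given in full. All that can be said is that weighing is not listed.

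**Conclusion.** The point holds as a minor dosing-safety correction. On the printed text, the Coartem age column omits 6-11 months (6 of 54 age-months) and lists exactly 5 years twice, with courses that differ by a factor of 2. Both follow from comparing the chart with the eligibility criteria and need no outside source.

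The practical harm is conditional: it arises only if the chart passes unchanged into the job aids and CHWs dose by age. Neither condition can be confirmed from the protocol, and the number of children affected cannot be stated. Whether the chart departs from the manufacturer or national guidelines cannot be checked here either.

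A reader might infer that a primary result or the comparison between arms is at risk. It is not: the Coartem primary outcome is receipt of the drug, the same chart serves both arms, and nothing in the documents points to a direction of bias. A process measure such as appropriate treatment (3.6, 5.5) would be touched only if Coartem dose is scored there, and the protocol does not say that it is.

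**What to change.** Before the CHW job aids in 4.10 are produced, have the responsible clinicians and the hospital pharmacist check the Coartem chart against the manufacturer and national guidelines that 4.11.2 names. Subject to that check:

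1. Start the age entry of the first row at 6 months, since its 5-14 kg band already gives 1 tablet twice a day.
2. Put exactly 5 years in one row only, and use the same boundary wherever age 5 is dosed.

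The corrected chart should be used in both arms. The cost is one edited age cell for the first change, at most one more for the second, and a short clinical check. Sample size, outcomes and analysis do not change.

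A rule on whether age or weight governs when they disagree is a separate decision. It has a real cost either way: scales and a weight field if weight governs, or some off-weight doses if age does. The two edits above do not depend on it.

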**4.12 Referral System**

The current referral system is based on verbal referral or at best, a handwritten note. This system will be improved. If during assessment, a CHW decides that a patient needs referral, he will give a start dose of the appropriate medication, if indicated, and will fill a standard referral form which will be in two parts. The CHW will complete the first part, which will provide information on the presenting signs and symptoms (and diagnosis), any treatment given and date and time of referral. He will then give a copy to the patient to be taken to the health facility. At the health facility, the second part of the referral form will be completed when the patient is discharged and given to the caregiver to be sent back to the CHW. This second part will contain information on date and time of arrival to the health facility, date of discharge from the health facility, final diagnosis, and treatment given at the health facility and follow up instructions. When the CHW receives this second part (the “feedback” form), he will update his records with the information and keep the form in a file. During community sensitization activities, NHCs and CPTs will be encouraged to arrange for transportation for referral cases. Referral of sick children to the health center is part of standard care. The research protocol attempts to improve the documentation and feedback

